## VERSION CONTROL

| Version | Issue date | Reasons for amendments; additional changes |
|---------|------------|--------------------------------------------|
| 1.0     | 05Jul2021  | Version 1                                  |

## LIST OF ABBREVIATIONS

|        |                                                            |
|--------|------------------------------------------------------------|
| AB     | Advisory Board                                             |
| AE     | Adverse Event                                              |
| CI     | Chief Investigator                                         |
| CRF    | Case Report Form                                           |
| CRN    | Clinical Research Network                                  |
| CTU    | Clinical Trials Unit                                       |
| DMC    | Data Monitoring Committee                                  |
| EHR    | Electronic Health Records                                  |
| FCP    | First Contact Practitioner                                 |
| GCP    | Good Clinical Practice                                     |
| HCP    | Health Care Professional                                   |
| HRA    | Health Research Authority                                  |
| IRAS   | Integrated Research Application System                     |
| ISF    | Investigator Site File                                     |
| ISRCTN | International Standard Randomised Controlled Trial Numbers |
| MSK    | Musculoskeletal                                            |
| NICE   | The National Institute for Health and Care Excellence      |
| NRS    | Numerical Rating Scale                                     |
| PCN    | Primary Care Network                                       |
| PI     | Principal Investigator                                     |
| PIC    | Participant Identification Centre                          |
| PIS    | Participant Information Sheet                              |
| PPIE   | Patient and Public Involvement and Engagement              |
| QA     | Quality Assurance                                          |
| QC     | Quality Control                                            |
| REC    | Research Ethics Committee                                  |
| RUG    | Research User Group                                        |
| SDV    | Source Data Verification                                   |
| SMF    | Study Master File                                          |
| SMG    | Study Management Group                                     |
| SMS    | Short Messaging Service                                    |
| SOP    | Standard Operating Procedure                               |
| SSI    | Site Specific Information                                  |

## STUDY SUMMARY

|                                       |                                                                                                                                                                                                                                                                                                                                                   |                                                                                                                                                                      |
|---------------------------------------|---------------------------------------------------------------------------------------------------------------------------------------------------------------------------------------------------------------------------------------------------------------------------------------------------------------------------------------------------|----------------------------------------------------------------------------------------------------------------------------------------------------------------------|
| Study Title                           | "Real world" pain outcomes and experiences of care (MIDAS-GP)                                                                                                                                                                                                                                                                                     |                                                                                                                                                                      |
| Internal Ref. Number (or short title) | MIDAS-GP
[Patient facing name: MIDAS-GP Study]                                                                                                                                                                                                                                                                                                 |                                                                                                                                                                      |
| Study Design                          | Observational Cohort Study                                                                                                                                                                                                                                                                                                                        |                                                                                                                                                                      |
| Study Intervention (where applicable) | N/A                                                                                                                                                                                                                                                                                                                                               |                                                                                                                                                                      |
| Study Participants                    | Adults aged 18+ years consulting general practice for a common musculoskeletal pain condition                                                                                                                                                                                                                                                     |                                                                                                                                                                      |
| Planned Sample Size                   | 
For patient-reported outcomes and experiences: 1,139 patients from 26 practices (completing a baseline questionnaire and consenting to further contact and individual record linkage)
 
For electronic health record (EHR)-only processes of care: 11,388+ patients from 26+ general practices (minimum of 150 patients per practice)
 |                                                                                                                                                                      |
| Treatment duration                    | N/A                                                                                                                                                                                                                                                                                                                                               |                                                                                                                                                                      |
| Follow up duration                    | 6 months (self-report outcomes); 12 months (EHR outcomes)                                                                                                                                                                                                                                                                                         |                                                                                                                                                                      |
| Planned Study Period                  | July 2021 – Mar 2025                                                                                                                                                                                                                                                                                                                              |                                                                                                                                                                      |
|                                       | Objectives                                                                                                                                                                                                                                                                                                                                        | Outcome Measures                                                                                                                                                     |
| Primary                               | To estimate the magnitude and direction of differences between potentially 'disadvantaged' and 'advantaged' groups of patients in their reported musculoskeletal health outcomes up to 6 months after consultation [patient-reported outcomes/experiences subcohort]                                                                              | 
Expected main outcomes:
 
MSK-HQ score
 
Pain intensity (0-10 NRS)
 
Work productivity and activity impairment (WPAI)
                          |
|                                       | To estimate the magnitude of between-practice variation in processes of care for adults consulting with a MSK pain condition [EHR-only processes of care]                                                                                                                                                                                         | 
Expected main outcomes:
 
Practice-specific rates of primary care (re)consultation, secondary care referral, opioid prescribing, musculoskeletal imaging
 |

## PLAIN ENGLISH SUMMARY

**AIM OF THE RESEARCH:** To provide new research evidence to inform efforts to reduce variation in the outcomes and experiences of care between different groups of patients with musculoskeletal pain and between different general practices.

**BACKGROUND:** Painful musculoskeletal conditions like back pain and osteoarthritis cause more disability in the general population than any other health conditions. Poorer communities and individuals appear to be hardest hit. In order to have a suitably 'joined up' response to this challenge we need accurate and meaningful joined up information on musculoskeletal health, risk, and care in local populations. This is what our study will try to address.

**DESIGN AND METHODS:** We will invite adults who have recently consulted their general practice with a painful musculoskeletal condition to tell us about their condition and their care. People will have the option of doing this through an online questionnaire (with support over the telephone, if needed) or by pen-and-paper questionnaire. If people agree, we will contact them again with short questionnaires up to 6 months later to understand if they have got better. We will also ask them if we can link their questionnaire responses with information held in their medical records so that we can piece together the type of care people are receiving with the kind of problem they have and the outcome of their care. We want to involve at least 26 general practices across North Staffordshire and Stoke-on-Trent, particularly those serving more deprived and ethnically diverse areas. Despite our best efforts, we know that not all people will agree to take part. So, to get a proper overview, a second part of this study will look at the overall levels of prescribing painkillers, referrals to hospital specialists, and other measures of musculoskeletal care for each general practice.

**PATIENT AND PUBLIC INVOLVEMENT:** We have a dedicated Patient Advisory Group who have already been involved in designing this study. They have:

- stressed the importance of looking seriously at inequalities in health and care
- suggested ways of raising awareness, maintaining interest in the study, and making it easier for a wide range of people to take part
- looked carefully at the questionnaires and suggested ways of making it more relevant and easier to complete

We will continue to work with this Group to monitor how the study is going, what the findings mean, and how best to share them with participants, the public, and other groups and maximise our chances of this research making a real difference.

**SHARING OUR FINDINGS:** We will look to produce:

- Written summary reports, graphs and tables for participating GP practices and community musculoskeletal services
- Press releases, briefings, articles, and interviews for local radio and newspapers
- A study website, institutional websites, and post messages on social media including Twitter, YouTube video
- Publications (to include public co-authors) including full report, executive summary and plain English summary, peer-reviewed journals, and local NHS and research newsletters
- Presentations at high-profile scientific and health policy conferences: NHS Evidence, Society for Academic Primary Care, Chartered Society of Physiotherapy, Public Health England

## SUMMARY STUDY FLOW CHART

[figure not shown]

## 1 BACKGROUND AND RATIONALE

Musculoskeletal (MSK) conditions are the main drivers of non-communicable disease disability burden in most countries and regions worldwide.[1] In England, they account for an estimated 21% of total years lived with disability,[2] 6.2 million working days lost,[3] 12-14% of all primary care consultations in people aged 15 years and over,[4,5] and the third largest programme budget for NHS healthcare expenditure.[6] The need for better information for chronic disease surveillance of MSK conditions has been highlighted by the Chief Medical Officer[7] and in successive Global Burden of Disease reports for England.[8,9] Public Health England's 5-year strategy for musculoskeletal health (2019-2024) includes a commitment to "high quality, accessible data and intelligence tools to support surveillance and reduce unwarranted variation of musculoskeletal conditions across the population pathway." [10]

Our MIDAS programme of research, funded by the Nuffield Foundation and Versus Arthritis, seeks to develop and evaluate a place-based system for population musculoskeletal health intelligence across North Staffordshire and Stoke-on-Trent ([Enriched data integration for population musculoskeletal health intelligence | Nuffield Foundation](#)).

The current study – an observational cohort study of the episode outcomes of patients presenting to general practice with a common, painful MSK conditions - is one component of this programme. It addresses an important priority for the NHS: to better integrate data from different clinical settings within the musculoskeletal clinical pathway in order to inform system wide changes that can reduce the burden of common MSK conditions. To date, meaningful data collected from population level surveys, primary care electronic health records and community service providers have not been co-ordinated and linked together to inform public health and primary care policy making.

In order to link data together, we plan to conduct a prospective patient cohort of adults consulting a healthcare professional (predominantly GP or First Contact Practitioner (FCP)) situated within participating GP practices, for a painful MSK condition. The data collected will come from one of three sources:

- (1) patient questionnaires: for measures of severity, impact, levels of knowledge, confidence, and understanding of their condition, experiences of care, and wider social determinants.
- (2) electronic medical record data: for recorded care (e.g. prescriptions, referrals, imaging, Fit Notes, repeat GP visits) and comorbidities
- (3) publicly available data on neighbourhood health, assets and deprivation and on healthcare service characteristics

By linking these sources of data we are seeking to create multi-level data on patient cohorts that enable us to better understand variations in, and determinants of, musculoskeletal outcomes in adults presenting to primary care with a common painful MSK condition. Our intention is for this study to impact on decisions about what information may be most useful and how it might be collected, linked, analysed, and disseminated within routine care.

## 2 AIMS AND OBJECTIVES

The **overall aim** of this prospective cohort study is to investigate variation and inequalities in patient-reported outcomes and experiences of care and the type of care received by adults presenting to general practice with a non-inflammatory musculoskeletal (MSK) pain condition. The study comprises two main components:

(a) Patient-reported outcomes/experiences: collection via online and offline surveys of patient-reported outcome and experience measures up to 6 months after consultation and, with individuals' consent, linkage to primary care electronic health record data and NHS Digital datasets and place-based information on wider determinants of health. While all eligible MSK consultants will be invited to participate in this component of the study, only a self-selected proportion are anticipated to take part in this study component.

(b) EHR-only processes of care: extraction and analysis of pseudonymised data from the primary care electronic health record on recorded processes of care for all eligible consecutive MSK consultants during the study period and prior to this. By descriptive analysis of record-level data on the total underlying target population this component will enable us to evaluate self-selection bias in the patient-reported outcomes/experiences subcohort, enable adequately powered investigation of variations between GP practices in recorded care, and extend our findings from a single snap-shot view in time.

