## **2.1. Primary objectives**

**2.1.1.** To estimate the magnitude and direction of differences between potentially 'disadvantaged' and 'advantaged' groups of patients in their reported MSK health outcomes up to 6 months after consultation [patient-reported outcomes/experiences subcohort]

**2.1.2.** To estimate the magnitude of between-practice variation in rates of primary care (re)consultation, secondary care referral, opioid prescribing, and musculoskeletal imaging for adults consulting with a MSK pain condition [EHR-only processes of care]

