## **2.2. Secondary objectives**

**2.2.1.** To estimate differences between potentially 'disadvantaged' and 'advantaged' groups of patients in their experiences of primary care MSK consultation [patient-reported outcomes/experiences subcohort]

**2.2.3.** To explore within-practice change in consultation prevalence and recorded management of MSK pain among adults presenting to general practice over time, including comparing current levels with those before COVID (i.e. pre-2020) [EHR-only processes of care]

**2.2.4.** To plot the flow of patients along different MSK care pathways and to define MSK service organisation characteristics for participating general practices and Primary Care Networks (PCNs) [patient-reported outcomes/experiences subcohort]

**2.2.5.** To produce new benchmarked data on processes and outcomes of care for MSK pain conditions at GP practice and PCN levels and to provide new insights into the credibility, validity, and persuasiveness of new visualisations of this MSK health intelligence and present these for feedback from key stakeholders

**2.2.6.** To explore the relationships between identified variations and inequalities in patient care, outcomes, and experiences and their association with wider determinants and organisational characteristics

**2.2.7.** To test case-mix adjustment methods for identifying outliers for recorded processes of care

**2.2.8.** To evaluate patterns of non-response and non-participation and their implications for bias in the above estimates

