## 6 STUDY PROCEDURES

### 6.1. Overview

Potential participants will be those consulting a participating general practice for a relevant MSK pain related problem during the study period. Relevant MSK pain-related consultations will be identified using a pre-specified SNOMED codelist. Eligible patients with an active mobile phone number will be invited via SMS text sent from the practice computer system to complete a web-based questionnaire, based on a secure server at Keele University. Patients without an active mobile telephone number at the practice will be posted a questionnaire for pen-and-paper completion via DOCMail, a secure remote document compilation, print and mailing solution. Follow-up questionnaires will be sent by Keele CTU at 3 and 6 months, with a brief questionnaire sent in the intervening months (SMS text or postal). All participants will be asked for informed consent to link their questionnaire responses to primary care electronic health record and healthcare datasets (e.g. hospital visits) held by NHS Digital. This “patient-reported outcomes/experiences subcohort”, providing individual-level, linked patient-reported and health record data, will be used to answer questions on variations in outcomes and experiences of care. Separately, pseudonymised information from primary care electronic health records will also be sought from all eligible patients consulting a participating practice with a relevant MSK pain condition during the study period and across the previous five years. These will be analysed and presented at the level of GP practice and PCN to add a wider, longer-term view of between-practice and between-PCN variation in care.

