- Keeping questionnaire length to a minimum[11,18]; presenting questions in a logical order; minimising cognitive burden of questions; explaining where possible the purpose of questions
- Raising awareness of the survey among the practice and registered patient population prior to going live; using reminders to encourage questionnaire completion[11,18]
- Collection of brief information in the questionnaire on important social characteristics (e.g. date of birth, sex, ethnicity, occupational class, financial strain) to help understand participation, care, and outcomes in under-served groups
- Using pseudoanonymised extracts from the GP clinical system to describe the characteristics of those invited to participate (e.g. Practice Code, Practice Name, Age, Sex, Lower Super Output Area (from postcode), Ethnicity, Method of Invite), as well as the characteristics and patterns of care of the total eligible population of MSK consultants to enable evaluation and possible modelling of selective participation

Those who participate in the study and return either a paper or online questionnaire will be given the opportunity to select a local charity that they would like us to make a donation to. At the end of the initial, 3-month and 6-month questionnaires, participants will be given a choice of four local charities to give to. For every returned baseline, 3-month and 6-month questionnaire £1 will be given to the charity specified by the participant.

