## 7.3. Statistical analysis plan

### 7.3.1. Patient reported outcomes and experiences

#### 7.3.1.1. Summary of baseline data and flow of patients

We will determine the percentage of eligible patients responding at baseline and descriptively compare responders to all eligible patients consulting during the recruitment time period by age, gender, type of musculoskeletal pain, general practice and PCN.

We will report summary statistics (mean and standard deviation, median and interquartile range or frequencies and percentages as appropriate) for each baseline and follow-up measure, overall and stratified by age, gender, and type of musculoskeletal pain. We will also weight responses by age,

gender, and type of musculoskeletal pain distribution of eligible patients to assess the potential impact of non-response on our estimates.

Missing data within responders at each time point should be low but we will use multiple imputation if there are items with >5% missing data.

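### The non-participation check fixed in section 7.3.1.1 compares and weights patient characteristics, so it cannot show whether the disadvantaged–advantaged contrast of objective 2.1.1 is distorted

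*Protocol*

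**What the plan says.** The first primary objective (Protocol 2.1.1) is a contrast: "To estimate the magnitude and direction of differences between potentially 'disadvantaged' and 'advantaged' groups of patients" in patient-reported outcomes up to 6 months.

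Three places deal with selective participation in general terms:
- Section 2, component (b), on the record-based data: "By descriptive analysis of record-level data on the total underlying target population this component will enable us to evaluate self-selection bias".
- Objective 2.2.8: "To evaluate patterns of non-response and non-participation and their implications for bias in the above estimates". The estimates listed above it include the group differences.
- Section 6.2 gives as a purpose of the pseudonymised extracts to describe the "characteristics and patterns of care of the total eligible population of MSK consultants to enable evaluation and possible modelling of selective participation". For those invited, it lists LSOA and ethnicity among the extracted items.

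Section 7.3.1.1 turns this into a method. The study will "descriptively compare responders to all eligible patients consulting during the recruitment time period by age, gender, type of musculoskeletal pain, general practice and PCN", and will weight responses by the age, "gender, and type of musculoskeletal pain distribution of eligible patients to assess the potential impact of non-response on our estimates". Section 7.3.1.2 weights on the same three variables. Of the EHR-only data, section 6.1 says: "These will be analysed and presented at the level of GP practice and PCN". The imputation in section 7.3.1.4 deals with loss after baseline, not with failure to join.

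**The concern.** The check is aimed at a different quantity from the one it has to protect. Comparing the make-up of responders with that of eligible patients, and weighting to the eligible distribution, speaks to overall levels. A difference between two groups is biased when the relation between health and response is not the same in both. That can happen while age, gender, pain type, practice and PCN all match. The variables that define disadvantage and are held on the record (ethnicity, area deprivation) are in neither the comparison nor the weights.

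The plan assumes 25% response at baseline, and section 6.2 itself says that people likely to be digitally excluded may be disadvantaged and have poorer outcomes. The section 7.3.1.1 check could therefore look clean while the baseline inequality is understated or overstated. Objective 2.2.8 would then go unanswered for the contrast in 2.1.1.

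**Working it through.** **1. The plan's own participation figures (section 7.1.1).**
- 7300 × 0.80 × 0.15 = 876 consulters per practice per year; 876 / 4 = 219 in 3 months; 219 × 26 = 5694 eligible.
- 5694 × 0.25 = 1423.5 baseline responders (stated 1424).
- 1423.5 × 0.80 = 1138.8 consenting to contact and linkage (stated 1139).
- 1138.8 × 0.50 = 569.4 at 6 months (stated 569).

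All four figures reproduce. Linked participants are 20% of eligible patients and 6-month responders 10%.

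**2. Distortion of the baseline contrast.** Inputs from section 7.1.1: SD 10, target difference 3 points, 25% response. Assumptions (the protocol gives none): MSK-HQ is normal within group; response is flat at 25% in the advantaged group; in the disadvantaged group it is *a* below and *b* above that group's own median, averaging 25%; response is unrelated to age, gender or pain type.

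Shift in the disadvantaged mean = −10 × √(2/π) × (a − b)/(a + b), with √(2/π) = 0.798.

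| a / b | (a − b)/(a + b) | Shift in contrast (points) |
|---|---|---|
| 27.5% / 22.5% | 0.10 | −0.8 |
| 30% / 20% | 0.20 | −1.6 |
| 35% / 15% | 0.40 | −3.2 |

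The sign reverses if healthier patients respond more. Identical selection in both groups gives 0; opposite selection doubles the figures. In every row the characteristics compared in 7.3.1.1 are unchanged, so weighting on them removes nothing.

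**3. The follow-up contrast.** Section 7.3.1.2 models 3- and 6-month MSK-HQ adjusted for baseline MSK-HQ. If response depends only on group and baseline score, the distribution of follow-up score given group and baseline is the same in responders as in everyone. A correctly specified linear model then still estimates the adjusted difference without bias. A simulation with 20% response above and 10% below the median in the disadvantaged group, flat response in the other, correlation 0.5 and a true adjusted difference of −3.0 moved the baseline contrast by +2.7 and returned an adjusted estimate of −3.00. The table therefore applies to the baseline model. The follow-up model is exposed only to selection on prognosis beyond baseline score.

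**4. What a direct check on recorded care could detect.** Compare the group difference in linked responders with that in all eligible patients. Responders are nested in the eligible set, so SE = √(V_sub − V_full), with V = p(1 − p) × [1/(Mq) + 1/(M(1 − q))] and M = 1139 or 5694. Assumed: outcome rate p = 40%, so p(1 − p) = 0.24; equal response in both groups.

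| Group share q | V_sub | V_full | SE (pp) | 95% half-width, 1.96 × SE | Detectable at 80% power, 2.80 × SE |
|---|---|---|---|---|---|
| 10% | 0.002341 | 0.000468 | 4.3 | 8.5 | 12 |
| 20% | 0.001317 | 0.000263 | 3.2 | 6.4 | 9 |
| 40% | 0.000878 | 0.000176 | 2.7 | 5.2 | 7 |

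Unequal response makes this worse. With 15% response in a 10% group, 569.4 × 0.15 × 0.80 = 68 are linked, against 5124.6 × 0.25 × 0.80 = 1025 in the other group. The SE is then 5.7 and the 80% threshold about 16 percentage points.

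**The case against.** **The records are already meant for this, and the rest is SAP detail.** A reader might infer that the recorded outcomes go unused for judging selection. The protocol does not support that: section 6.2 names patterns of care for evaluating and possibly modelling selective participation, section 2 gives the bias evaluation to the record component, and 2.2.8 covers the group differences. A separate SAP may add detail. What stands against the objection is that section 7.3 is itself headed as the statistical analysis plan. It names the comparison variables and the weights, and says the weighting will assess the impact of non-response. That is a stated method which does not reach the stated objective, rather than silence.

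**The size is assumed, and does not carry to follow-up.** Both parts are right. No passage supports a particular selection strength, so only a range including zero can be given. A reader might infer that the 3- and 6-month inequality is off by the same amount; because those models adjust for baseline MSK-HQ, it need not be.

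**The remedy may miss the problem.** A 0.27 SD shift in MSK-HQ would move a 40% outcome by only about 2 to 5 percentage points if the latent correlation is 0.2 to 0.5 (assumed), which is about one SE or less in a 10% group. This stands as a limit: the check can expose gross distortion, but a null result would not rule out bias.

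**Conclusion.** The point holds in a limited form. The check in 7.3.1.1 omits ethnicity and deprivation and, by its construction, cannot show whether the 2.1.1 contrast is distorted, although 2.2.8 promises an answer and section 6.2 names the data that could help.

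The baseline contrast could be off by about 0.8 to 3.2 points under one-sided selection, and by nothing if selection is alike in both groups. These sizes rest on assumed response patterns and the protocol's SD of 10. They show that the bias could reach the 3-point target, not that it will. It would also be too much to conclude that recorded care can correct the MSK-HQ estimate: the protocol gives no mapping from one to the other. The change is a worthwhile, inexpensive improvement.

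**What to change.** In section 7.3.1.1, for objective 2.2.8:
1. Add ethnicity and LSOA deprivation to the comparison of responders with all eligible patients.
2. For each main recorded outcome (reconsultation, referral, opioid prescribing, imaging) and each stratifier on the record (age, sex, ethnicity, LSOA deprivation), report the group difference in (i) all eligible patients of the recruiting practices and windows, (ii) linked responders unweighted and (iii) linked responders weighted. Give (ii) − (i) and (iii) − (i) with 95% confidence intervals.
3. Where these depart from zero, attach a caveat to the MSK-HQ inequality for that stratifier. Do not derive a bias-shifted MSK-HQ range from them.
4. State the limits: recorded care is a proxy for MSK-HQ; financial strain and job title come from the questionnaire and are not covered; precision is poor for small groups, so a null result is not proof of no bias.

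The sponsor should confirm that ethnicity and LSOA are extracted for all eligible patients: section 6.2 lists them for those invited, while section 6.4 does not list them for the EHR-only extract. Otherwise the cost is a few extra models on data already planned. Non-responders need not be re-identified.
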